# HOPE-trial: hemiarthroplasty compared to total hip arthroplasty for displaced femoral neck fractures in the elderly-elderly, a randomized controlled trial

**DOI:** 10.1186/s12891-015-0763-3

**Published:** 2015-10-19

**Keywords:** Femoral neck fracture, Hemiarthroplasty, Total hip arthroplasty, Harris hip score, Randomized clinical trial, Octagenerians

## Abstract

**Background:**

A femoral neck fracture (FNF) is a common cause of suffering and premature death in the elderly population. Optimizing the treatment for improved outcome and a reduced need for secondary surgery is important both for the patient and the society. The choice of primary total or hemiarthroplasty in patients over eighty years are controversial. We hypothesized that total hip arthroplasty has an equal or better outcome in patient-reported outcome compared with hemiarthroplasty.

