**Fig. 1 Fig1:**
[figure not shown]
Flow diagram

We hypothesized that a total hip arthroplasty results in superior hip function and health-related quality of life compared to to hemiarthroplasty in healthy and cognitively intact patients aged above 80 years treated for a displaced femoral neck fracture. The secondary outcome measurement includes mortality, complications and reoperations.

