### Sample size

Prior to the commencement of the study, a two-sided power analysis has been performed. We will test the null hypothesis that the mean Harris hip scores for the two groups will be equal. We assume that a mean difference of 10 points (standard deviation, 15 points) [4] in the Harris hip score is the smallest effect that will be clinically relevant. We calculate that a total of 80 patients (40 in each group) will have a power of 80 % to yield a significant result.

This calculation also allows a 80 % power to prove non-inferiority (non- difference) of the secondary endpoint EQ-5D with a sample of 40 patients in each group with the assumption of an EQ-5D value of 0.73 with standard deviation 0:18. The significance level was set at a conservative 2.5 % (p <0.025) because we have two sample size calculations. We will include 60 patients in each group (120 total) to allow for loss to follow-up.

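### The article states its hypothesis as equal-or-better, as superiority and (for EQ-5D) as non-inferiority, but plans only difference tests, so what a null result may claim is not fixed

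*Protocol article*

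**What the plan says.** The article states the aim in four ways.

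- **Abstract, Background:** "We hypothesized that total hip arthroplasty has an equal or better outcome in patient-reported outcome compared with hemiarthroplasty". A true difference of zero satisfies this.
- **Main Background, last paragraph:** "We hypothesized that a total hip arthroplasty results in superior hip function and health-related quality of life" compared with hemiarthroplasty. A true difference of zero contradicts this, for both outcomes.
- **Sample size, HHS:** "We will test the null hypothesis that the mean Harris hip scores for the two groups will be equal", with the remark that "a two-sided power analysis has been performed". The relevant effect is given as follows: "We assume that a mean difference of 10 points (standard deviation, 15 points) [4] in the Harris hip score". The word superior does not appear here, but a two-sided test of equal means is a difference (superiority) design.
- **Sample size, EQ-5D:** the same 40 per group is said to give 80 % power for non-inferiority, with absence of a difference added in brackets as a synonym. A mean of 0.73 and SD of 0.18 are given, but no margin. EQ-5D is called secondary here, although the Abstract and Endpoints and follow-up list it as primary.

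Statistics plans Student's t-test for HHS and EQ-5D, and ANCOVA for the primary endpoint. Both are difference tests.

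**The concern.** Equal-or-better and superior are different hypotheses that need different decision rules. Superiority is judged by whether the interval for the difference excludes zero. Equal-or-better is judged by whether the lower confidence limit lies above a margin declared in advance. The article gives only the first kind of test, beside hypotheses of both kinds.

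Suppose HHS at 2 years shows no significant difference. The main Background's hypothesis is then unsupported, while an author could present the Abstract's hypothesis as borne out. Nothing in the text says which statement governs. For EQ-5D the conflict sits in the body itself: the main Background expects superior quality of life and Sample size aims at non-inferiority. The trial's headline conclusion could therefore be settled by which sentence is cited after the data are seen.

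**Working it through.** **Inputs.** From Sample size: HHS difference 10, SD 15, 40 per group (60 randomised per group to allow for losses), two-sided test, significance level 2.5 %. Results at 5 % are also shown, because the stated power does not match 2.5 %. The 60-per-group figures assume no losses.

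**1. The plan's own figure.** Sample size says "a total of 80 patients (40 in each group) will have a power of 80" per cent. The standard error of the difference is 15 × √(2/40) = 3.354, so the noncentrality is 10/3.354 = 2.98. The noncentral t distribution gives 83.8 % power at two-sided 5 % and 75.5 % at two-sided 2.5 %. The stated 80 % is not reproduced exactly at either level. That is a separate matter, and the conclusion here does not depend on it.

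**2. Width of the HHS interval.** Half-width = t(1 − α/2, 2n − 2) × 15 × √(2/n).

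| n per group | SE | two-sided 2.5 % | two-sided 5 % |
|---|---|---|---|
| 40 | 3.354 | 2.286 × 3.354 = 7.67 | 1.991 × 3.354 = 6.68 |
| 60 | 2.739 | 2.270 × 2.739 = 6.22 | 1.980 × 2.739 = 5.42 |

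**3. What a non-significant result leaves open.** At 40 per group and 2.5 %, any observed difference between −7.67 and +7.67 is non-significant. A result just short of significance against total hip arthroplasty has a lower limit near −7.67 − 7.67 = −15.3, beyond the protocol's own 10-point relevant effect. The lower limit stays above −10 only if the observed difference exceeds −10 + 7.67 = −2.33. So observed differences from −7.67 to −2.33 are non-significant yet compatible with a 10-point deficit. At 60 per group the corresponding range is −6.22 to −10 + 6.22 = −3.78.

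**4. Chance of non-significance when total hip arthroplasty is truly 10 points worse** (noncentral t):

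| n per group | two-sided 2.5 % | two-sided 5 % |
|---|---|---|
| 40 | 24.5 % | 16.2 % |
| 60 | 8.5 % | 4.8 % |

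**5. The same data judged by a margin rule.** The article declares no HHS margin. Assume, for illustration only, that the 10-point relevant effect served as one, with a true difference of 0. A lower limit from the 97.5 % interval (one-sided 1.25 %) would then give power of about 76 % at 40 per group and 91 % at 60. A true 10-point deficit would be wrongly passed in 1.25 % of trials. With an assumed margin of 5 points, power falls to 23 % and 34 % (normal approximation). Whether equal-or-better is attainable thus depends on a margin that is not stated.

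**6. EQ-5D.** The standard error at 40 per group is 0.18 × √(2/40) = 0.0402. For 80 % power at a true difference of 0, the margin would have to be (1.960 + 0.842) × 0.0402 = 0.113 at one-sided 2.5 %, or (2.241 + 0.842) × 0.0402 = 0.124 at one-sided 1.25 %. Neither value appears in the article, so the non-inferiority power claim cannot be tied to a hypothesis.

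**The case against.** The strongest reply is that equal-or-better occurs in one sentence of an abstract, which sets no test. It names patient-reported outcome rather than HHS, and may be a loose summary of the two aims in Sample size: a difference on HHS and non-inferiority on EQ-5D. For HHS, the main Background, Sample size and Statistics agree with one another. A t-test also yields a confidence interval, and 10 points is on record as the smallest relevant effect, so there is a yardstick even if it is not called a margin. Rules for reporting a null result often sit in an analysis plan, which is not shown.

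Much of this stands. A reader might infer that the trial plans to declare equality from a non-significant HHS test. The article does not say so, and its nearest wording, which equates non-inferiority with no difference, concerns EQ-5D. A reader might also take the 24 % as a rate of false equality claims. It is the type II error of the difference test, and would be a false-equality rate only if every non-significant result were called equal, which is not a stated rule.

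The reply does not remove the inconsistency. If the Abstract summarises the two aims in Sample size, the main Background still contradicts it by claiming superiority on both outcomes. The contradiction is in the current text and is not a detail left to another document.

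**Conclusion.** The point holds as an inconsistency in the stated hypotheses that affects both primary endpoints. The HHS test itself remains valid; what is not fixed is the claim that may be drawn from it. Non-significance alone cannot support equality, no non-inferiority margin is declared for HHS, and the EQ-5D aim differs between the main Background and Sample size.

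For scale, under SD 15 and two-sided 2.5 %, the HHS half-width is 7.7 points at 40 per group and 6.2 at 60. A 10-point deficit would go undetected in 24 % and 8.5 % of trials. At two-sided 5 % these become 16 % and 4.8 %, so the conclusion does not hinge on how the significance level is read. The documents do not support the stronger statement that a false equality claim is planned. They leave room for one.

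**What to change.** State one hypothesis per primary endpoint and use it in the Abstract, Background, Sample size and Statistics.

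- **HHS at 2 years:** superiority, two-sided, as the main Background and Sample size already imply. Align the Abstract with it.
- **EQ-5D at 2 years:** reconcile the main Background with Sample size. Choose either superiority, or non-inferiority with a justified margin fixed before unblinding and a confidence-limit rule. Drop the gloss that equates non-inferiority with no difference, and give EQ-5D the same primary or secondary status throughout.
- **Null results:** report the difference with its confidence interval and do not call it equal. Allow an equal-or-better claim only if the lower confidence limit lies above a margin declared before unblinding.

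For HHS this changes wording only; the test and the number of patients stay as they are. For EQ-5D, if non-inferiority is chosen, the power statement must be recalculated for the declared margin. The sponsor gives up the option of claiming equality from a null test.

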**Methods/Design:**

A prospective, randomized, single-blinded trial will be conducted. We will include 120 patients, 80 years of age and over with an acute (<36 h) displaced femoral neck fracture. The patients will be randomized in a 1:1 ratio to either total hip arthroplasty or hemiarthroplasty. The primary endpoints are Harris hip Score and EQ-5D. Secondary endpoints include pain measured with visual analogue scale, surgical time, reoperations, complications and radiological measurement of erosion in patients operated with hemiarthroplasty. Follow-up will be performed postoperatively after three months, 1, 2, 4 and 10 years.

**Discussion:**

To our knowledge, this is the first randomized controlled trial comparing total hip arthroplasty and hemiarthroplasty for displaced femoral neck fracture in patients age 80 years and over.

**Trial registration:**

Clinicaltrial.gov: NCT02246335

## Background

How femoral neck fractures in aged patients should be treated are determined by the degree of displacement, age, functional demands, surgeon preference and risk for complications associated with cognitive function and degree of physical fitness [1–7]. The main methods of choices are internal fixation, hemiarthroplasty and total hip arthroplasty. Internal fixation is the main alternative for young patients with displaced intracapsular fractures and in frailest elderly patients who are not medically fit for prosthesis surgery [2, 8]. Most surgeons seem to recommend that hemiarthroplasty is the preferred treatment for elderly patients with low functional demands in the absence of arthritic changes in the hip [9]. However, despite extensive research during the last decades and a number of randomized controlled studies that has been published comparing the types of arthroplasty in the treatment of displaced femoral neck fractures - the question remains if there is any advantage in replacing the healthy acetabulum with a prosthetic cup in the healthy, cognitive intact elderly patient [10–15]. A number of published studies have suggested that total hip arthroplasty may produce better hip patient reported outcomes compared with hemiarthroplasty. However, the majority of studies conducted are made for a subgroup of patients that are active and living in their own homes without cognitive alteration. The study settings are, with few exceptions [12, 14, 15], made up of a relative large population of patients below 80 years of age. Nevertheless, even a patient with low demands seems to benefit from a total hip arthroplasty. Reported advantages of hemiarthroplasty over total hip arthroplasty are a reduced rate of dislocation, shorter operation times including less blood loss and less technically demanding surgery [14-17]. Surgeons favouring total hip arthroplasty rely on the tendency for improved hip function. The longevity and level of activity of todays elderly increases the risk for protrusion of the femoral head in the acetabulum and the need for revision operation. Despite the more extensive surgery during total hip arthroplasty there has not been any detectible difference in mortality in comparison to hemiarthroplasty [1, 18].

**Fig. 1 Fig1:**
[figure not shown]
Flow diagram

We hypothesized that a total hip arthroplasty results in superior hip function and health-related quality of life compared to to hemiarthroplasty in healthy and cognitively intact patients aged above 80 years treated for a displaced femoral neck fracture. The secondary outcome measurement includes mortality, complications and reoperations.

## Methods/Design

### Study design

A randomized controlled trial will be conducted. The study will be carried out from 2009–2026 (inclusion period 2009–2016) at the Orthopaedic Department of Danderyd Hospital in collaboration with the Karolinska Institute. The study will be conducted in accordance with the ethical principles of the Declaration of Helsinki. The Ethics Committee of the Karolinska Institute approved the study. The trial is initiated, designed, and performed as an academic investigation and registered at ClinicalTrials.gov (number NCT02246335). The guidelines of the CONSORT Statement will be followed [19].

### Study population

All patients with a femoral neck fracture who are admitted to Danderyd Hospital during the inclusion period will be screened for participation in the study and those who agree to participate and provide written informed consent will be included. The inclusion criteria are an acute displaced femoral neck fracture (Garden stage III or IV) that had been sustained within the previous thirty-six hours, an age of eighty years or more [20], an ability to walk indoors and outdoors with or without the help of walking aids and an absence of cognitive dysfunction (Pfeiffer test 8–10 points) [21]. Exclusion criteria includes patients with osteoarthritis or rheumatoid arthritis in the fractured hip, pathologic fractures, non-walkers, severe cognitive impairment (Pfeiffer test 0–7), and contraindications for surgery by other reasons (ulcers, severe somatic illness, severe bleeding disorder) and those who were unsuitable to participate in the trial for any other reason (i.e. psychiatric disease, alcoholism).

A detailed inclusion and exclusion list is presented in Table 1. The inclusion period is planned from 2009–2016. End of study (EOS) will be at the last included patient’s last visit in 2026 (Fig. 1, Table 2).

**Table 1 Tab1:** Detailed inclusion and exclusion criteria

Inclusion criteria	
1. Age above 80 years.	
2. Acute (<36 h) displaced femoral neck fracture (Garden ≥3).	
3. Independent walking ability with or without walking aids.	
4. Pfeiffer test 8–10 points.	
Exclusion criteria	
1. Osteoarthritis or rheumatoid arthritis in the fractured hip	
2. Pathologic fractures	
3. Non-walkers	
4. Cognitive impairment (Pfeiffer Test 0–7)	
5. Contraindications for surgery by other reasons (ulcers, severe somatic illness, severe bleeding disorder).	
6. Unsuitable to participate in the trial for any other reason.

**Table 2 Tab2:** Secondary endpoints

No.	Measurement	Follow-up time
1	Baseline data including height, weight, medical history, physical examination	Screening
2.	Pain Numerical Rating Scale (PNRS)	Screening, 3 months, 1, 2, 4, 6 and 10 years
3.	Complications	Screening, 3 months, 1, 2, 4, 6 and 10 years
4	Reoperations	Screening, 3 months, 1, 2, 4, 6 and 10 years

### Treatments

Half of the patients will receive a cemented hemiarthroplasty with a modular unipolar head. The other half will receive a cemented total hip arthroplasty with a 32-mm femoral head articulating on a cemented highly cross-linked polyethylene acetabular component. The same stem and the same bone cement will be used for both groups. The operations will be performed either by a consultant orthopedic surgeon or by a registrar with assistance from a consultant. A direct lateral approach will be used [22]. The direct lateral approach is performed through a midline incision over the greater trochanter through the subcutaneous fat and the fascia. The anterior one-third of the gluteus medius insertion and gluteus minimus insertion on the tip of greater trochanter are detached. Excision of the anterior hip joint capsule is performed from the base to the acetabulum. The fractured femoral neck is planed and the caput femoris is extracted. During closure of the wound, the detached part of muscle gluteus medius and minimus is re-attached to the trochanter. Prophylactic cloxacillin is administered 30 min before surgery, and the cloxacillin also another 3 times over 24 h postoperatively. Low-molecular weight heparin will be administered for 30 days postoperatively. The patients are mobilized according to a standard physiotherapy program, and full weight bearing with the use of crutches are encouraged. Plain x-rays of the pelvis and hip will be taken postoperatively and at follow-up.

### Randomization and blinding

Patients will be randomized in a 1:1 ratio to hemiarthroplasty or total hip arthroplasty using concealed envelopes in batch sizes of 10. Randomization will be stratified for gender and patients will be blinded for the assigned treatment during the first two years of follow-up. Patients will not be allowed to view x-rays. Ward staff and physiotherapists are aware of allocations but are mindful that patients are blinded and are encouraged not to speak to patients about allocation. The physiotherapy, nor any other in-hospital care, do not differ between the two groups. In addition, the blinding will be controlled for at the 1 and 2 year follow-up where patients will be asked what group they think they belong to. The blinding is ended at the 2-year follow-up and in case of any hip related serious adverse events such as reoperations for any reasons.

### When and how to withdraw subjects from the trial

Should a subject request or decide to withdraw from the study, all efforts will be made to complete and report the observations as thoroughly as possible up to the date of withdrawal. For withdrawn subjects the last post-baseline observation will be carried forward. In a case of withdrawal of full consent, the subject will be followed according to the routine standard follow-up of arthroplasty patients at our institution, including regular clinical examinations and radiographic follow-up visit at the operating surgeon every 2–3 years.

### Endpoints and follow-up

The primary endpoint variable will be patient-reported functional hip status assessed with Harris hip score [23–25] and health related health-related quality of life assessed by the EQ-5D (EuroQoL) at 2 years. EQ-5D uses five dimensions: mobility, self-care, usual activity, pain/discomfort and anxiety/depression [26].

Secondary endpoints include functional scores at the other follow-up times and pain in the operated hip evaluated with VAS (Visual Analogue Scale [27], surgical time and blood loss, erosion of the acetabular cartilage in patients treated with hemiarthroplasty (evaluated according to Baker et al. [11]).

The study period is 10 years. Follow-up will be performed at 3 months, 1, 2, 4, 6 and 10 years. First study results will be reported after the last patient enrolled in the study has been followed for 2 years.

### Data quality assurance

The study progress and study conduct will be monitored before, during and after the study to ensure that ICH-GCP, regulatory requirements, and all aspects of the protocol are followed. A digital case report form (CRF) will be used throughout the study. The medical records and other documents will be reviewed for verification of agreement with data on the CRF. The subject has a right for a protection against invasion of privacy. In this study, each subject will receive a unique identification number, which will be linked to the CRF. The data will then be blinded correspondingly in all data analyses. However, the study monitor, auditor, representative from any regulatory authority, as well as the appropriate Ethical Committee are permitted to review the subject’s primary medical records including laboratory test result reports, ECG reports, admission and discharge summaries, AE and SAE reports occurring during the study.

### Sample size

Prior to the commencement of the study, a two-sided power analysis has been performed. We will test the null hypothesis that the mean Harris hip scores for the two groups will be equal. We assume that a mean difference of 10 points (standard deviation, 15 points) [4] in the Harris hip score is the smallest effect that will be clinically relevant. We calculate that a total of 80 patients (40 in each group) will have a power of 80 % to yield a significant result.

This calculation also allows a 80 % power to prove non-inferiority (non- difference) of the secondary endpoint EQ-5D with a sample of 40 patients in each group with the assumption of an EQ-5D value of 0.73 with standard deviation 0:18. The significance level was set at a conservative 2.5 % (p <0.025) because we have two sample size calculations. We will include 60 patients in each group (120 total) to allow for loss to follow-up.

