### Statistics

The analyses will be performed on the basis of the intention-to-treat principle, and all patients who are allocated to either group will be included in the analysis, regardless of actual surgery performed. Descriptive statistics (means and standard deviations) will be used to describe the patient characteristics and outcome variables at the measurement points. We will use the Student’s t-test and Levene’s test for comparison of Harris hips score and EQ-5D between the groups. An analysis of covariance (ANCOVA) of the primary endpoint will also be used to reduce variance, adjusted for exposure variable (total hip arthroplasty/hemiarthroplasty) and stratification (male/female). For subjects that withdrawn from the study before completion, the data from the last observation will be carried forward (imputed). The analyses will be performed with SPSS 22.0 for Windows (SPSS, Chicago, Illinois) statistical software.

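### The 80 % power for EQ-5D non-inferiority is undefined because no margin is given, and the claim does not agree with the planned test or the superiority hypothesis

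*Protocol article*

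**What the plan says.** Three parts of the protocol article bear on how EQ-5D will be judged.

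- **Sample size.** The Harris hip score calculation is superiority-type: it tests equality of means, using "a mean difference of 10 points (standard deviation, 15 points" as the smallest relevant effect. The section then claims "80 % power to prove non-inferiority (non- difference) of the secondary endpoint EQ-5D with a sample of 40 patients in each group", under the "assumption of an EQ-5D value of 0.73 with standard deviation 0:18" (the SD is read here as 0.18). On the level it says: "The significance level was set at a conservative 2.5 % (p <0.025) because we have two sample size calculations". It opens by saying that "a two-sided power analysis has been performed", but gives no sidedness for the non-inferiority test. Planned enrolment is 60 per group, to allow for loss to follow-up.
- **Statistics.** The only comparison named for EQ-5D is: "We will use the Student’s t-test and Levene’s test for comparison of Harris hips score and EQ-5D between the groups". An ANCOVA of the primary endpoint is added. There is no margin, no confidence-interval criterion and no non-inferiority test.
- **Hypotheses.** The Background, in the paragraph after Fig. 1, says: "We hypothesized that a total hip arthroplasty results in superior hip function and health-related quality of life compared to" hemiarthroplasty. The Abstract says: "We hypothesized that total hip arthroplasty has an equal or better outcome in patient-reported outcome compared with hemiarthroplasty".

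**The concern.** The power of a non-inferiority test is the probability of ruling out a deficit as large as a stated margin. Sample size, SD and significance level do not fix that probability without the margin, and a mean of 0.73 does not supply it. The article therefore publishes a result together with every input except the one that defines it.

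The rest of the plan does not fill the gap. The Background sets a superiority hypothesis for quality of life, the Sample size section speaks of non-inferiority and equates it with non-difference, and the Statistics section names a t-test without a criterion. A reader cannot tell which conclusion the EQ-5D analysis is meant to support.

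EQ-5D is part of the primary endpoint in the Endpoints and follow-up section, although the Sample size section calls it secondary. If the comparison is non-significant, the parenthetical gloss leaves room to present that as non-difference backed by 80 % power.

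**Working it through.** **Inputs.** From Sample size: SD 0.18, 40 per group (60 enrolled), level 2.5 %, power 80 %. Assumed here: true difference 0 for the non-inferiority power, and margins of 0.05 to 0.15. The article does not say whether 2.5 % is one-sided or two-sided for EQ-5D, so one-sided 2.5 % and one-sided 1.25 % (two-sided 2.5 %) are both shown. Normal-approximation steps are written out, and the noncentral-t results follow.

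**Step 1: try to reproduce the 80 %.** The standard error of the difference with 40 per group is 0.18 × √(2/40) = 0.0402. Power is Φ(margin/0.0402 − z), where z is the one-sided critical value. The margin is missing, so the stated figure cannot be computed.

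**Step 2: how far the power can range** (40 per group, noncentral t):

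| Assumed margin | one-sided 2.5 % | one-sided 1.25 % |
|---|---|---|
| 0.05 | 23 % | 15 % |
| 0.08 | 50 % | 39 % |
| 0.10 | 69 % | 58 % |
| 0.12 | 84 % | 76 % |
| 0.15 | 96 % | 92 % |

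For example, a margin of 0.05 at one-sided 2.5 % gives 0.05/0.0402 − 1.960 = −0.72, and Φ(−0.72) ≈ 24 % (23 % by t).

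**Step 3: solve backwards for the margin that gives 80 %.** Margin = 0.0402 × (z + 0.842).

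- One-sided 2.5 %: 0.0402 × (1.960 + 0.842) = 0.113; 0.114 by t.
- One-sided 1.25 %: 0.0402 × (2.241 + 0.842) = 0.124; 0.126 by t.
- One-sided 5 %, for comparison: 0.0402 × (1.645 + 0.842) = 0.100; 0.101 by t.

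**Step 4: what a non-significant t-test would mean.** This is the probability that a two-sided 2.5 % t-test of zero difference is non-significant when total hip arthroplasty is truly worse on EQ-5D (SD 0.18, noncentral t). The standard error with 60 per group is 0.18 × √(2/60) = 0.0329.

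| True deficit | 40 per group | 60 per group |
|---|---|---|
| 0.05 | 85 % | 77 % |
| 0.075 | 66 % | 49 % |
| 0.10 | 42 % | 22 % |

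Normal check for 0.10 with 40 per group: 2.241 − 0.10/0.0402 ≈ −0.24, and Φ(−0.24) ≈ 40 % (42 % by t).

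**The case against.** Several stronger readings are tempting, and the article does not support them.

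- **That the 80 % is false.** It is unverifiable, not disproved. An assumed margin of 0.12 at one-sided 2.5 % gives 84 % with 40 per group, and 0.114 gives 80 %.
- **That the claim contradicts the 2.5 % level.** A round margin of 0.10 fits 40 per group only at one-sided 5 %, but the 0.10 is an assumption made here. The article gives neither a margin nor the sidedness for EQ-5D.
- **That the investigators will declare non-difference from a large p-value.** No such rule is stated. The gloss in the Sample size section may be loose wording. It makes the reading possible, not planned.
- **That a t-test can never serve non-inferiority.** The confidence interval from a t-based analysis can, if compared with a margin. What is lacking is the margin and the criterion.
- **That the implied margin is too wide.** In SD units it is 0.114/0.18 = 0.63 to 0.126/0.18 = 0.70, close to the 10/15 = 0.67 used for the Harris hip score. Nothing in the article transfers a threshold from one scale to the other.

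Two further defences carry some weight. The analysed number may be nearer 60 than 40, because last observations are carried forward, and the Step 4 figures are then clearly smaller. The Abstract's equal-or-better wording is also compatible with non-inferiority followed by superiority.

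Condensation of a full protocol into an article, or an unseen analysis plan, would excuse missing detail. It does not excuse a published power that has no meaning without the missing input. Nor does it reconcile the superiority hypothesis in the Background with the non-inferiority claim.

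**Conclusion.** The point holds in this form: the article states a non-inferiority power for EQ-5D without the margin that defines it, plans a comparison without a non-inferiority criterion, and hypothesises superiority elsewhere. Followed as written, the plan cannot deliver the non-inferiority conclusion for which it claims power.

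The undefined figure covers about 23 % to 96 % at one-sided 2.5 %, across assumed margins of 0.05 to 0.15. If non-significance were read as non-difference, a true deficit of 0.10 would be missed 42 % of the time with 40 per group and 22 % with 60. For a deficit of 0.075 the figures are 66 % and 49 %.

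These figures rest on the article's SD of 0.18. The non-inferiority powers also assume a true difference of zero. The margins and deficits are illustrations, not values from the article.

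**What to change.** Delete the EQ-5D non-inferiority power claim from the Sample size section. Test EQ-5D for superiority, as the Background hypothesis says, and bring the Abstract's wording into line. Report the difference between groups with a 97.5 % confidence interval, which matches a two-sided 2.5 % level. State that a non-significant result will not be interpreted as equivalence or non-inferiority.

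Keep a non-inferiority claim only if the margin used in the pre-study calculation can be documented. In that case state the margin, the direction, the one-sided alpha, the confidence-interval criterion and the power it actually gives. A newly chosen margin is hard to defend: inclusion runs from 2009 to 2016, the article appeared in October 2015, and postoperative X-rays show investigators the allocation.

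The cost is wording. The stated EQ-5D power is withdrawn or may become less favourable, and no new patients are needed.
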